# Rationale and design of the GLADE study: a randomized, multicenter, double-blind, placebo-controlled trial evaluating the safety and efficacy of gestrinone subdermal bioabsorbable pellet in endometriosis-related pelvic pain

**DOI:** 10.1080/07853890.2025.2527352

**Published:** 2025-07-11

**Keywords:** Endometriosis, pelvic pain, subcutaneous pellet, gestrinone, R-2323

## Abstract

**Background:**

Pelvic pain secondary to endometriosis is a disabling condition. There are multiple treatments available, with variable endpoints. No prospective controlled studies were carried out evaluating subdermal pellets of gestrinone in this population.

**Methods:**

One hundred participants with documented deep infiltrative endometriosis who underwent surgery without satisfactory response will be randomly assigned (1:1) to either gestrinone 85 mg subdermal bioabsorbable pellets or placebo. Both arms will receive levonorgestrel-releasing intrauterine system (LNG-IUS 12). The treatment duration will be 6 months, with baseline, 3 months and 6 months clinical visits. The primary endpoint is a combination of serious adverse events (SAEs) accumulated within 6 months of insertion of the gestrinone or placebo pellet and collected through spontaneous reports and clinical findings. They include death, threat or risk to life, need for hospitalization, prolongation of pre-existing hospitalization, permanent disability or damage, congenital anomaly; or significant medical occurrences such as venous thromboembolism. The primary safety outcome will be the percentage of patients who do not experience SAEs 6 months after randomization. Androgenization, changes in laboratory exams and in pelvic pain intensity as well as quality of life (SF-36 and EHP-30 questionnaires) will be further evaluated. Daily data on uterine bleeding patterns and the use of pain relief medication will be remotely collected using an App. Pharmacokinetics profile of gestrinone pellet will be characterized.

**Conclusion:**

This is the first multicenter randomized controlled trial to evaluate the safety, tolerability and pharmacokinetics profile of subdermal gestrinone pellets and might inform clinical practice for treating these patients.

**Administrative Information:**

GLADE trial is registered at ClinicalTrials.gov (NCT05570786). This is an investigator-initiated research supported by Biòs Farmacêutica.

## Introduction

Pelvic pain is a disabling condition for women of reproductive age, negatively impacting their quality of life and work efficiency. Doctors frequently neglect it despite its estimated worldwide prevalence ranging from 5.6 to 26.6 [1,2]. Pelvic pain is considered a symptom of multifactorial origin in which endometriosis is the leading gynecological cause that affects 5–10% of women in their reproductive years. It means around 176 million women with endometriosis worldwide [3].

Surgical and hormonal treatments with variable endpoints are available and are still considered a significant challenge for medicine. Recommendations from different medical guidelines for managing the disease include surgery or a combination of surgical and pharmacological strategies [4–6]. Hormone therapy includes progestogens, anti-progestogens, combined oral contraceptives, gonadotrophin releasing hormone (GnRH) agonists, GnRH antagonists, the levonorgestrel intrauterine system (LNG-IUS), danazol and aromatase inhibitors. The choice of treatment for endometriosis must consider the severity of the symptoms, extent, and location of the lesions, comorbidities, age, intention to become pregnant, adverse drug events, and contraindications. Surgical treatment is indicated in the case of severe and disabling symptoms without improvement after the pharmacological treatment. However, post-surgery recurrence rate of painful symptoms is 21.5% after 2 year and 40–50% after 5 years of the surgery [4–6]. The direct costs for treatment of endometriosis are significant. The Brazilian Unified Health System (SUS) in 2021 registered 26,400 medical appointments and 8,000 hospitalizations for endometriosis with limited access to multifunctional teams specialized in endometriosis and longtime waiting for a surgery [7]. In this context, pharmacological treatment for endometriosis is prominent.

A Cochrane Review about progestagens and anti-progestagens for pain associated with endometriosis showed gestrinone as anti-progestogen (i.e. a substance that prevents cells from making or using progesterone) and one of the first drugs for the treatment of endometriosis and myomas [8]. Gestrinone acts centrally on the hypothalamic pituitary system by suppressing the release of luteinizing hormone (LH) and follicle-stimulating hormone (FSH). Both continuous progestogens and continuous gestrinone are effective therapies for the treatment of painful symptoms associated with endometriosis. There was no overall evidence of a benefit of one oral progestogen over another. However, this conclusion must be treated with caution due to the lack of placebo-controlled studies [8]. The World Endometriosis Society (WES) [5] and the European Society of Human Reproduction and Embryology (ESHRE) [6] guidelines discuss the use of gestrinone as a possible medication for the treatment of endometriosis-related pain. Gestrinone should be used for those whom other treatments have proven ineffective despite potential treatment-associated adverse effects [5]. However, there is still a lack of quality evidence from placebo-controlled randomized clinical trials.

GLADE (Gestrinone peLlet AnD Endometriosis) Study is a decentralized, patient-centered, multicenter, randomized, double-blind, parallel, placebo-controlled clinical study to primarily evaluate the safety and tolerability of subdermal gestrinone bioabsorbable pellet in the treatment of pelvic pain secondary to endometriosis. With this study, we hope to advance the knowledge about gestrinone subdermal pellets, their possible side effects, pharmacokinetics profile and their ability to alleviate pain and improve quality of life of women with endometriosis.

### Gestrinone compound profile

#### Physicochemical properties and pharmaceutical formulation

3-ethyl-17-hydroxy-18,19-dinor-17α-pregna-4,9,11-trien-20-yn-one, known as gestrinone, ethylnorgestrienone or R-2323 is a synthetic derivative of 19-nortestosterone developed in 1960 originally as a contraceptive and has been studied as a treatment for leiomyoma and endometriosis [9]. It is a compound with the molecular formula C21H24O2 and a molecular weight 308.4.14.

#### Mechanism of action

The mechanism of action of gestrinone is complex and multimediated. It inhibits folliculogenesis and acts on the hypothalamic-pituitary axis, preventing the increase in gonadotropins (FSH and LH) in the middle of the ovulatory cycle, causing estrogen inhibition, anovulation, and amenorrhea. It has an affinity for progesterone and estrogen receptors and a low affinity for androgen receptors while at the same time inducing a reduction in the expression of progesterone receptors [10]. It can reduce the production of SHBG (Sex-hormone binding globulin), which causes an increase in blood levels of free testosterone and progesterone, leading to the emergence of their androgenic effects [11].

#### Metabolization and excretion

After oral administration, gestrinone has a serum half-life of around 24 h, undergoing active hepatic metabolism essentially by hydroxylation, and its metabolic conjugates are eliminated through urine (40–45%) and feces (30–35%) [12].

#### Side effects

Most of the adverse effects of gestrinone are due to its androgenic activity and include acne, skin and hair seborrhea, mild hirsutism, edema, weight gain, voice changes, androgenetic alopecia, and clitoral hypertrophy. The drug showed an embryotoxic effect on animals, with a risk of androgenization of female fetuses. It reduces HDL concentrations, and it is recommended to monitor cholesterol and liver transaminase levels in hyperlipidemic patients and glucose levels in diabetic patients. Other effects related to inhibition of the pituitary-ovarian axis may include menstrual disorders and amenorrhea, hot flashes, sweating, breast reduction, changes in libido, vaginal dryness, and emotional fluctuations [13].

#### Clinical evidence

Previous clinical studies evaluating gestrinone and endometriosis are scarce. A study by Diaz et al. (1977) assessed the contraceptive effect of the subdermal gestrinone implant in Chilean women for 12 months, as well as the emergence of possible adverse events. The authors reported a potent inhibitory effect on fertility in patients, which was accompanied by an increase in transaminases and the appearance of acne, headaches, and hirsutism [14].

Oral treatment with gestrinone (2.5 to 5 mg twice a week) induced improvement in symptoms associated with endometriosis without the need for daily administration of the drug, which is usually required in similar conservative therapies, representing an option for treatment of the disease. Furthermore, patients treated vaginally tend to have fewer androgenic adverse events such as acne, seborrhea, and weight gain than those treated orally [15].

Worthington et al. (1993) evaluated the effects of oral gestrinone (1.25 and 2.5 mg twice a week for 6 months) on some metabolic parameters of women with laparoscopically confirmed endometriosis. The study concluded that the drug was effective in treating the disease without inducing any loss of bone density but caused unfavorable effects on serum lipids and lipoproteins that were reversed 6 months after the end of treatment [16].

A randomized clinical study involving 43 women with endometriosis compared 6 months of treatment with gestrinone (5 mg per week) or buserelin nasal spray (300 µg every 8 h) with a 5-year follow-up and found that both treatments were effective in remitting endometriosis. There were reports of acne and vascular events such as edema and heaviness in the lower limbs in the group that received gestrinone [17].

In 1996, The Gestrinone Italian Group Study compared oral treatment with gestrinone and leuprolide acetate for pelvic pain in women with endometriosis in a randomized, double-blind clinical study, concluding that both were equally effective. However, gestrinone did not affect the patient’s bone density despite inducing fluctuations in serum lipid values [18].

Trials evaluating gestrinone in the form of a gel for vaginal application (Gestrinone Pentravan^®^) for the treatment of endometriosis have also been carried out and report positive effects of the drug in relieving refractory pain [19].

Subdermal gestrinone bioabsorbable pellet could be a safe and effective alternative for treating endometriosis-associated pelvic pain and minimize adverse events observed with oral administration.

### Objectives

#### Primary objective

To evaluate the safety and tolerability of the use of gestrinone subdermal bioabsorbable pellet in women with pelvic pain secondary to endometriosis who underwent surgery without satisfactory response.

#### Secondary safety objectives

To evaluate the potential for androgenization of the use of gestrinone subdermal bioabsorbable pellet in women with pelvic pain secondary to endometriosis who underwent surgery without satisfactory response.

#### Other exploratory objectives

To compare the use of gestrinone subdermal bioabsorbable pellet versus placebo pellet on participant satisfaction, change in pelvic pain intensity, use of pain relief medication, uterine bleeding pattern and quality of life. Additionally, the pharmacokinetic profile (PK) of gestrinone will be characterized in a subgroup of participants.

## Patients and methods

The report of this study protocol follow the SPIRIT (standard protocol items: Recommendations for interventional trials) 2013 guidelines [20].

### Study design

The first participant was included on February 25th 2023 and the last patient last visit is estimated for April 2025. The laboratory analysis for measurement of gestrinone plasma levels are undergoing. We will carry a decentralized, patient-centered, multicenter, randomized, double-blind, parallel, placebo-controlled study. The study will be conducted in 7 research centers in Brazil (hospital and clinics).

The study protocol has several innovations to increase participant recruitment and retention such as the organization of disease awareness campaigns and the participation of a patient representative as member of the Trial Steering Committee. Participant representative provided information about the burden of the disease and the impact of the treatment through a patient perspective that enabled the inclusion of patient-reported outcomes in the study protocol. An App will be used to remotely collect diary registries about uterine bleeding pattern and use of analgesics for pain relief and other adverse events in real time. These protocol innovations are depicted in Figure 1.

**Figure 1. F0001:**
[figure not shown]
Protocol innovations.

The study protocol was approved by the Institutional Review Board (IRB – Comitê de Ética Hospital Leforte, CAAE: 64457622.5.1001.5485, Approval Number: 5.748.523, Dated: November 9^th^, 2022). The study protocol was approved by the institutional review boards at all research sites. Written informed consent will be obtained from all patients before any study procedure is applied. The study was registered at ClinicalTrials.gov (NCT05570786). The first participant was included on February 25^th^ 2023 and the last patient last visit is estimated for April 2025.

The study protocol is composed of two stages: 1) Main protocol: randomized, double-blind, parallel, placebo-controlled, *N* = 100 participants, treatment duration and follow-up: 6 months; 2) Extension-PK (EXT-PK): open-label, *N* = 15 participants (subgroup of participants who concluded the main protocol and accepted to receive the treatment; follow-up: 6 months. The study design is depicted in Figure 2.

**Figure 2. F0002:**
[figure not shown]
Study design.

Participants eligible for the main stage of the study will be randomized into one of the treatment arms:Experimental: Insertion of the levonorgestrel-releasing intrauterine system (LNG-IUS 12, Kyleena^®^) and gestrinone subdermal bioabsorbable pellet (85 mg)Comparator: Insertion of the levonorgestrel-releasing intrauterine system (LNG-IUS 12, Kyleena^®^) Kyleena^®^ levonorgestrel-releasing intrauterine system and subdermal implant of placebo bioabsorbable pellet

The insertion of the levonorgestrel-releasing intrauterine system (LNG-IUS 12, Kyleena^®^) is necessary as a contraceptive method for all study participants. LNG-IUS (LNG-IUS 12) has been developed for up to 5 years of use with an average release rate of ∼12 μg/24 h over the first year [21]. Clinical assessments will be recorded at recruitment (baseline), 3 and 6 months after pellet insertion. Assessment of the primary outcome will be carried out 6 months after insertion of the gestrinone pellet.

Participants will be invited to an extension phase (open-label) of the study to provide additional long-term safety data (EXT-PK). A subgroup of 15 participants at the end of 6 months of the main stage of the study who accept to participate in the extension phase will receive an insertion of a gestrinone pellet (85 mg), and the serum concentration of gestrinone will be monitored to characterize its pharmacokinetic profile (PK). Clinical assessments will be recorded at recruitment (baseline), 1, 3 and 6 months after pellet insertion. Blood sampling for PK study will be conducted.

Bioabsorbable gestrinone pellets are produced and marketed by Biòs Farmacêutica following standardized procedures and current legislation. Pellets containing a placebo will be prepared under the same conditions as those containing the product ingredient. Biòs Farmacêutica will donate all pellets used in this study.

GLADE is an investigator-initiated project. Biòs Farmacêutica funded the trial but was not involved in the study design, data collection, analysis, interpretation, writing of the manuscript, or decision to publish. The Trial Steering Committee designed the study protocol and is monitoring the trial’s progress. The first draft of the manuscript was written by the first and the last author and revised based on comments from all the authors. No writing assistance was provided.

### Patients

The study will enroll 100 women with refractory pain control who underwent surgery for endometriosis at least 3 months ago and who had a histologically confirmed diagnosis of deep infiltrative endometriosis. Eligible participants are women with pelvic pain secondary to endometriosis surgically treated with refractory symptoms, independent of pain intensity. .Endometriosis-associated pelvic pain includes dysmenorrhea, dyspareunia, dysuria, dyschezia, and nonmenstrual pelvic pain.

Study participants have a medical history of indication for surgery as an option to reduce endometriosis associated-pain after having been failed to standard hormone treatment (combined hormonal contraceptives, progestogens, GnRH agonists or GnRH antagonists). Surgeries were conducted to fully eliminate endometriotic lesions from both the posterior compartment and anterior compartment, as well as from bowel compartment whenever present.

Detailed eligibility criteria are listed in Table 1.

**Table 1. t0001:** Study eligibility criteria.

Inclusion criteria
1. Willingness to provide informed consent
2. Woman aged between 18 and 50 years
3. Body weight between 50 ± 5 kg and 90 ± 5 kg
4. Pelvic pain secondary to endometriosis surgically treated with refractory symptoms, independent of pain intensity
5. Deep infiltrative endometriosis documented by biopsies (histopathological examination)
6. Last endometriosis surgery at least 3 months before randomization
7. Not planning to become pregnant within 12 months after the screening visit or be surgically sterilized
8. Absence of changes in the breast (BI-RADS 1 and BIRADS-2 classification) documented by an imaging report (mammogram for women aged > 40 years or bilateral breast ultrasound for women aged < 40 years) performed less than 12 months before randomization
9. Agreement not to use other hormones (estrogens, androgens and progestins) in any pharmaceutical form during the study
Exclusion criteria
1. Chronic severe disorders, including metastatic malignancies, end-stage renal disease with or without dialysis, clinically unstable heart disease, or any other disorder that, in the opinion of the investigator, excludes the participant from the study
2. Suspected or confirmed diagnosis of immunodeficiency based on medical history and/or physical or laboratory examination
3. Other medical or psychiatric conditions, including recent laboratory abnormalities (within the last 12 months) that may increase risks to the study participant or, at the discretion of the investigator, make the participant inappropriate for the study
4. Personal history of thromboembolic events
5. Use anticoagulant medication
6. Contraindication to the use of hormonal contraceptives
7. Suspected or confirmed pregnancy
8. Breastfeeding
9. Current or recurrent pelvic inflammatory disease or other conditions that increase the risk of pelvic infections
10, Postpartum endometritis or septic miscarriage in the last 3 months
11. Abnormal uterine bleeding of unknown etiology
12. Congenital or acquired uterine anomalies, including fibroids (leiomyomas or fibromas) that cause distortion of the uterine cavity
13. Uterine or cervical malignancy
14. Suspected or confirmed diagnosis of estrogen-dependent neoplasm, including breast cancer
15. Cervicitis or vaginitis, including bacterial vaginosis or another uncontrolled lower urinary tract infection
16. Cervical dysplasia
17. Active liver disease or dysfunction
18. Benign or malignant liver tumors
19. Allergy or intolerance to levonorgestrel, gestrinone or any other ingredient or component of the Kyleena^®^ formulation or hormonal pellets
20. Previously inserted intrauterine device or levonorgestrel-releasing intrauterine system that has not been removed
21. History of recent trophoblastic disease and continued high HCG levels
22. Bacterial endocarditis
23. Hyperandrogenism at the time of randomization, defined by: hirsutism: Ferriman-Gallwey score ≥ 8; clitoromegaly: defined by the Clitoral index ≥ 35 mm^2^, acne: defined by the IGA scale (Investigator’s global assessment) grade 5 – severe inflammatory acne dominates the area and there is a large number of comedones, pustules, papules and cystic acne; alopecia with sequelae of scalp thinning
24. Diagnosis of polycystic ovary syndrome
25. Participation in another pharmacotherapeutic or investigational medical device study within 30 days prior to the start of study treatment
26. Tobacco Use
27. Use of testosterone-derived hormones and analogues in the last month

Potential participants will be recruited by publicizing the study by doctors in their clinics, through social media, and the Science Valley Research Institute website in the study tab by answering a volunteer questionnaire. All the materials for recruitment purposes will be approved by the local IRB.

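### Table 1's hormone rules leave out GnRH analogues and aromatase inhibitors and set almost no interval off earlier therapy, so tests against baseline can read wear-off as a pellet effect

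*Protocol article*

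**What the plan says.** Four parts of the protocol article bear on this point.

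- **Hormone use during the study.** Table 1, inclusion criterion 9: "Agreement not to use other hormones (estrogens, androgens and progestins) in any pharmaceutical form during the study".
- **Hormone use before the study.** Table 1, exclusion criterion 27: "Use of testosterone-derived hormones and analogues in the last month". Exclusion criterion 20 rules out a "Previously inserted intrauterine device or levonorgestrel-releasing intrauterine system that has not been removed", with no interval since removal. Exclusion criterion 25 has a 30-day window, but it concerns taking part in other studies. Inclusion criterion 6 sets at least 3 months since surgery and says nothing about hormones in that time.
- **What counts as hormone therapy.** The Introduction's list opens with "Hormone therapy includes progestogens, anti-progestogens, combined oral contraceptives, gonadotrophin releasing hormone (GnRH) agonists, GnRH antagonists" and ends with "GnRH antagonists, the levonorgestrel intrauterine system (LNG-IUS), danazol and aromatase inhibitors". The Patients section says that surgery was indicated "after having been failed to standard hormone treatment (combined hormonal contraceptives, progestogens, GnRH agonists or GnRH antagonists".
- **How baseline is used.** The Statistical analysis section defines baseline as pre-treatment. It compares scores and indices with baseline by paired t-test and Wilcoxon test, and laboratory changes and other secondary outcomes by paired Wilcoxon test.

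Hormone history is collected at screening (Gynecological assessment), and pre-study medication is recorded (Record of pre-study and concomitant medications). Neither section restricts use.

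**The concern.** The article treats GnRH analogues and aromatase inhibitors as treatments for the disease under study, but its eligibility table names neither. For estrogens and most progestins, the table restricts use during the study without requiring time off them beforehand.

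Two consequences follow. First, baseline may be measured under an earlier therapy, or while its effect is fading. Change from baseline then combines the loss of the old drug with the effect of the new pellet. Randomization does not protect a within-participant comparison from this. The exposed measures are also ones on which the article expects gestrinone to act: it describes reduced SHBG, higher free testosterone, lower HDL and amenorrhea.

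Second, an unlisted agent started after randomization could alter pain or bleeding, possibly more often in one arm, without clearly breaching a stated criterion.

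**Working it through.** **Step 1: set the lists side by side.**

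| Therapy | Recognised in the article as endometriosis hormone therapy | Named in inclusion 9 (during study) | Lookback before baseline |
|---|---|---|---|
| Combined contraceptives (estrogen and progestin) | Introduction, Patients | yes | none |
| Progestogens | Introduction, Patients | yes | none, except any caught by exclusion 27 |
| LNG-IUS | Introduction | yes, as a progestin | removal only (exclusion 20) |
| GnRH agonists and antagonists | Introduction, Patients | no | none |
| Aromatase inhibitors | Introduction | no | none |

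The article describes gestrinone as a 19-nortestosterone derivative. Exclusion 27 might therefore be read to reach progestins of that family, but not estrogens, other progestins, GnRH analogues or aromatase inhibitors.

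**Step 2: which outcomes use a baseline value.** The primary outcome, the share of women free of SAEs, does not. Testosterone, SHBG and lipids (secondary safety) and pain and bleeding (exploratory) are compared with baseline or reported as change.

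**Step 3: size of the baseline problem.** The article gives no share of women affected, no effect size and no SD, so it has no figure to reproduce. What follows is illustration. From the article: 100 women, 1:1, possible 10% dropout, so n = 50 × 0.9 = 45 per arm; two-sided 0.05. Assumed: a share f of women carry over at baseline, their VAS score shifts by d cm as the effect fades, the SD of change is otherwise 2.5 cm, and there is no true change.

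- Bias in mean change = f × d.
- SD of change = √(2.5² + f(1−f)d²).
- Noncentrality = bias / (SD/√45). The rejection rate comes from the noncentral t distribution with 44 degrees of freedom.

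| f | d (cm) | Bias (cm) | SD (cm) | Noncentrality | Rejection rate |
|---|---|---|---|---|---|
| 0.1 | 2 | 0.2 | √6.61 = 2.57 | 0.52 | 0.08 |
| 0.2 | 2 | 0.4 | √6.89 = 2.62 | 1.02 | 0.17 |
| 0.3 | 2 | 0.6 | √7.09 = 2.66 | 1.51 | 0.32 |
| 0.5 | 2 | 1.0 | √7.25 = 2.69 | 2.49 | 0.68 |

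At f = 0.2, the rate runs from 0.08 (d = 1) to 0.30 (d = 3). At f = 0.3 and d = 2, it runs from 0.24 (SD 3) to 0.43 (SD 2). The shift need not favour the pellet: loss of an effective earlier drug would raise pain and could hide a real benefit.

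**Step 4: unlisted agents started after randomization.** Assume a true difference of 1.5 cm, SD 2.5 cm and 45 per arm. The standard error is 2.5 × √(2/45) = 0.527, and power is Φ(1.5/0.527 − 1.96) = 0.81. In an extreme case, 20% of placebo women and no gestrinone women start an agent worth 2 cm. The expected difference is then 1.5 − 0.2 × 2 = 1.1 cm, and power is Φ(1.1/0.527 − 1.96) = 0.55. Nothing in the article says that such uptake occurs.

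**The case against.** The case on the other side has real force.

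- **Current use is not shown.** A reader might infer that many women were on hormones at screening because all had received them. The Patients section places the failed therapy before surgery, and surgery was at least 3 months before randomization. It says nothing about use at screening. This stands.
- **Randomization balances prior use.** A reader might infer that the comparison of arms is biased. Chance imbalance in a factor not used for stratification is ordinary sampling variation, which standard errors already reflect. This stands: the baseline problem belongs to within-participant tests.
- **The wording may be broader than it looks.** The article files GnRH analogues under hormone treatment, so the phrase on other hormones could cover them, with the parenthesis only giving examples. This stands in part. The parenthesis reads more naturally as a definition, and an aromatase inhibitor is not itself a hormone.
- **When the study begins matters.** If it begins at consent, a woman taking a combined contraceptive up to the day of randomization breaches inclusion 9, and only carry-over remains for her.
- **The per-protocol set may already remove such women.** A reader might infer that it cannot. Its definition excludes significant violations and gives breach of inclusion criteria as one instance, so it is open rather than closed.
- **The full protocol may list prohibited drugs.** It may, and investigator discretion could block some cases. However, the article presents Table 1, with 9 inclusion and 27 exclusion criteria, as the detailed criteria. The point concerns what that table fixes.
- **Within-arm change is already mixed.** Every woman receives the LNG-IUS just before the pellet, so a washout alone would not make the paired tests interpretable. This stands, and it favours comparing arms.

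**Conclusion.** The point holds in limited form. As written, Table 1 does not exclude GnRH analogues or aromatase inhibitors at entry or during the study, and it asks for no interval off estrogens or most progestins before baseline. Combined with paired tests against baseline, this lets wear-off be taken for a pellet effect on secondary safety measures (testosterone, SHBG, lipids) and exploratory ones (pain, bleeding).

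The size cannot be fixed from the article. The rejection rates above rest wholly on assumed carry-over, shift and SD, and with no carry-over the problem disappears. The documents do not support a claim that a large share of women entered on hormones, that these agents are expressly permitted, that the between-arm contrast is biased at baseline, or that the primary SAE outcome is affected. The matter should be put right in the analysis, but it does not threaten the main result.

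**What to change.** **Text.** The sponsor should reconcile the Introduction, the Patients section and Table 1 on which hormone therapies inclusion 9 and exclusion 27 cover. No class list or washout length is proposed here. With the first inclusion in February 2023 and the last visit estimated for April 2025, rewording cannot change who entered.

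**Analysis of the data in hand.**

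1. From the hormone history and pre-study medication records, derive hormone use at screening, with class and stop date, and report it by arm.
2. For change in hormones, lipids, bleeding and pain, base conclusions on between-arm comparisons adjusted for hormone use at screening (yes/no), rather than on within-arm paired tests.
3. Before unblinding, classify on-study use of GnRH analogues or aromatase inhibitors as a significant deviation for the per-protocol set. If unblinding has already taken place, report the rule as post hoc.

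**Cost.** One extra covariate and a slightly smaller per-protocol set. The article says that the source records are collected, so no new data collection should be needed.
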